#### Anthropometric measurements (health impact pathway 4)

Anthropometric measurements will be collected from children under five years of age to assess the prevalence of undernutrition in relation to household agricultural production. Interviewers will use tared weighing scales, stadiometers, and length boards (all provided by Seca, Germany) to measure weight, standing height, and recumbent length, respectively. Each measurement will be taken twice by trained interviewers, with discrepancies checked and the mean value used for analysis. Detailed protocols follow those of Mank et al., who conducted anthropometric assessments in the same study region between 2017 and 2019 [30,49]. All measurements will be taken at the beginning of the harvest season, a period typically marked by reduced household food availability and increased food insecurity.

All measurements will be taken at the onset of the harvest season, a time typically characterized by diminished household food availability and heightened food insecurity.

### Data analysis

To examine the cascading effects of heat exposure on farmers’ work capacity and its subsequent impact on child nutrition, we will apply a multi-level analytical approach. Descriptive statistics – including measures of central tendency (mean, median) and dispersion (standard deviation, interquartile range) – will be calculated for each variable. Data distribution, outliers, and potential correlations will be visually assessed using histograms, box plots, and scatter plots.

Analyses will be stratified by age and gender to explore subgroup-specific differences in the effects of heat exposure. The analytical framework – detailing variables, data sources, measurement units, and their classification as continuous or categorical – is presented in Table 1. In addition, a Directed Acyclic Graph (DAG) will be constructed to visualize causal relationships and confounding factors affecting work capacity, agricultural productivity, and child nutritional status (see analytical framework: Figure 5 and Table 1).

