### Study participants and sample size

Participants will be randomly selected from both HDSS sites and will include subsistence farmers as well as children residing in their households. A farmer is defined as an individual whose primary occupation is agriculture, evidenced by the active cultivation of at least one food crop, with household livelihood primarily dependent on agricultural production.

The primary outcome variable is heart rate (beats per minute, bpm), used as a physiological proxy for heat-related strain in farmers. Heart rate reflects both physical exertion during agricultural labor and cardiovascular responses to heat stress, making it a key metric for assessing workload intensity and thermal burden. However, as heart rate increases can result from both physical exertion and heat exposure, the study will account for cardiac drift, which refers to the gradual increase in heart rate over time due to prolonged exertion in hot conditions. To differentiate between workload-related heart rate elevations and heat-induced cardiovascular strain, the following strategies will be applied:
Step data and GPS tracking will provide context for exertion levels during work activities.Time-of-day analysis will help distinguish between work-related and heat-related heart rate increases.Cross-referencing heart rate with environmental data (WBGT, temperature, humidity) will enable more precise differentiation between exertion-driven and heat-induced cardiac responses.

To estimate an appropriate sample size for the H2H pilot study, a power analysis is conducted for comparing means between two independent groups:$$n=\frac{2{\left(Z_{\alpha /2}+Z_{\beta }\right)}^{2}\times \sigma^{2}}{\delta^{2}}$$$$n=\frac{2{\left(Z_{\alpha /2}+Z_{\beta }\right)}^{2}\times \sigma^{2}}{\delta^{2}}$$

Where:
n is the sample size required per group.Z_α/2_ is the critical value associated with a desired alpha level (commonly set at 0.05 for a 95- Z_β_ is the critical value associated with the desired power of the test (commonly set at 0.80, yielding a Z_β_ value of 0.84).σ is the standard deviation of the outcome variable, which in this case is the bpm difference.δ is the expected difference in means between the two groups.

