A sample size of 63 participants per group is estimated to detect a mean difference of 5 bpm in heart rate with 95% confidence and 80% statistical power. To accommodate potential attrition and inter-individual variability, the H2H study will enroll a total of 210 participants across 25 villages within the HDSS sites during the feasibility phase.

In the Nouna HDSS, the H2H study is nested within a cluster randomized controlled trial (cRCT) evaluating the effectiveness of cool roof coatings as a passive home cooling intervention (DRKS trials registry number DRKS00023207) [46]. Cool roof coatings are designed to reflect solar radiation and exhibit high thermal emittance, thereby reducing indoor temperatures [47].

The cRCT includes 600 households, with 300 households randomly assigned to receive the cool roof intervention and 300 serving as controls. For the H2H study, farmers will be equally sampled from both intervention and control households to ensure balanced exposure conditions. The H2H study does not treat the cool roof intervention as a direct proxy for heat exposure but considers it a potential modifier of recovery following occupational heat stress.

This nested design facilitates the investigation of both direct and indirect heat-related pathways [1]: direct exposure during agricultural work – analyzing physiological responses, work capacity, and productivity; and [2] post-exposure recovery at home, examining whether improved indoor thermal environments enhance recuperation and influence subsequent health and labour outcomes.

While the cool roof cRCT focuses on the effectiveness of home cooling, the H2H study is primarily concerned with occupational heat exposure. Nevertheless, the interaction between workplace heat stress and home-based recovery conditions is a central component in understanding the cumulative effects of heat on health and productivity over time.

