#### Heat – outdoor and indoor temperatures and humidity (health impact pathway 1)

To evaluate how housing characteristics and microclimatic conditions influence individual heat exposure, we will conduct a descriptive analysis of indoor and outdoor temperature and humidity, with a particular focus on differences between households with and without cool roofs. This analysis will quantify thermal and humidity gradients across housing types and environments, offering insight into how structural factors influence indoor microclimates and outdoor heat stress conditions.

To ensure a comprehensive characterization of environmental exposure, the following components will be examined:
Daily and seasonal temperature fluctuations, enabling the identification of peak heat stress periods across the agricultural calendar.Indoor – outdoor temperature and humidity differentials, stratified by roof type, ventilation characteristics, and other household attributes, to assess how built environments mediate exposure.The influence of humidity, which plays a critical role in perceived heat stress and modulates physiological responses, especially under high ambient temperatures.

These environmental variables will be statistically summarized using measures of central tendency and dispersion (mean, median, standard deviation, interquartile range), and visualized via time series plots, box plots, and heat maps. Stratified comparisons will also be conducted by region, household type, and season to identify spatial and temporal patterns in heat exposure.

Findings from this microclimate analysis will be integrated into the broader analytical framework (see Figure 5 and Table 1), enabling linkage of environmental conditions with outcomes such as physiological strain, labor capacity, and agricultural productivity. This component is essential for informing both the SEM-based mediation models (Section 2.5.1) and the machine learning approaches (Section 2.5.2), providing environmental context for predictive modeling.

In addition, we will assess how natural variability in environmental parameters – including diurnal temperature ranges, humidity shifts, and extreme weather events – contributes to heat stress dynamics. These factors will be included as covariates or interaction terms in regression and SEM models, ensuring that environmental heterogeneity is appropriately accounted for in downstream analyses of heat-related impacts.

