#### Work capacity and physiological response (health impact pathway 2)

To further quantify the relationship between heat exposure and farmers’ work capacity, we will apply a combination of regression models and machine learning techniques. These approaches complement the broader analytical framework by enabling the detection of both linear and non-linear associations between environmental conditions and physiological responses.

Key heat exposure variables – indoor and outdoor temperature, humidity, and Wet Bulb Globe Temperature (WBGT) – will be modeled against continuous physiological indicators such as heart rate, activity levels, and sleep patterns. Linear mixed-effects models will be used to account for within-subject variability and repeated measures, with random effects specified at the individual level to capture heterogeneity in exposure and response. These models will incorporate covariates such as socioeconomic status and farming intensity to control for confounding.

Model validation will involve standard diagnostic tools including residual and Q – Q plots to assess normality, and Variance Inflation Factor (VIF) analysis to detect multicollinearity. In parallel, cross-validation and residual error analysis will be employed to test model robustness and predictive accuracy. Sensitivity analyses will explore how natural variations in environmental conditions – particularly fluctuations in temperature and humidity – affect the stability and reliability of the modeled outcomes.

To enhance the physiological assessment of energy expenditure and physical effort, we will deploy the Renkforce GP-102 GPS Logger, which includes an integrated pedometer function. These devices will collect location and movement data every 15 minutes, allowing for the estimation of energy expenditure based on distance traveled, travel speed, terrain changes, and rest intervals.

Time spent in agricultural fields will be georeferenced, with GPS data linked to each participant’s unique ID and merged with socio-demographic characteristics, field boundaries, and movement patterns. This enables a comprehensive analysis of how mobility and environmental exposure interact to shape work capacity.

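### Whether the heat effect differs by age and gender is assigned to stratified analyses, which give no estimate or test of the difference

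*Protocol article*

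**What the plan says.** The Data analysis section of the protocol article gives aim and method in one sentence: "Analyses will be stratified by age and gender to explore subgroup-specific differences in the effects of heat exposure". It names no test, no age bands, no age-by-gender cells and no rule for comparing the strata.

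Interaction terms are planned in one place, the analysis section on indoor and outdoor temperature and humidity (pathway 1): "These factors will be included as covariates or interaction terms in regression and SEM models". The factors meant there are environmental: daily temperature range, shifts in humidity and extreme weather.

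The analysis section on work capacity and physiological response (pathway 2) gives the model for the heat slope: "Linear mixed-effects models will be used to account for within-subject variability and repeated measures". On adjustment it says: "These models will incorporate covariates such as socioeconomic status and farming intensity to control for confounding". Age and gender are not among the examples. The section on structural equation modelling describes no multi-group model and no moderation by age or gender.

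**The concern.** A model fitted within one stratum asks whether that stratum's slope is zero. No such model has equality of the slopes as its null hypothesis. The method named therefore does not by itself answer the question it is given.

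Without a stated contrast, the easy reading is to compare verdicts: an effect found in women and not in men is taken as a difference. Two strata with the same true slope can give opposite verdicts simply because each holds only part of the information. The study wants its results to inform targeted adaptation, so a false subgroup difference could be carried forward.

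**Working it through.** **The plan's own figure.** The section on study participants and sample size uses n = 2(Z_α/2 + Z_β)²σ²/δ² per group. Alpha is given as "desired alpha level (commonly set at 0.05 for a 95"; the text breaks off there, and Z_α/2 makes it two-sided, so 1.96. Power is "commonly set at 0.80, yielding a Z_β_ value of 0.84". The result is: "A sample size of 63 participants per group is estimated to detect a mean difference of 5 bpm in heart rate". The standard deviation is not stated. Solving for it gives σ = 5 × √(63/2) / (1.960 + 0.842) = 10.02. With σ = 10, n = 2 × (1.96 + 0.84)² × 100 / 25 = 62.7, which rounds up to 63. The figure reproduces, but it concerns one comparison of two group means, not the heat slope and not strata.

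**Inputs for the check.**
- Two-sided alpha of 0.05, from the article.
- Pooled power of the heat slope: not stated, so assumed, from 80% to 99.99%.
- Share f of the information held by the larger stratum: not stated, so assumed, 0.5 or 0.7.
- True slopes equal in the two strata, and each stratum read by its own test against zero.

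**Formulas** (normal approximation).
- Pooled noncentrality: λ = 1.96 + z(power).
- Stratum noncentrality: λ√f and λ√(1 − f).
- Stratum power: p = Φ(λ_s − 1.96) + Φ(−λ_s − 1.96), where λ_s is the stratum's noncentrality.
- Probability that exactly one stratum is significant: p₁(1 − p₂) + p₂(1 − p₁).

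**Worked case, 80% pooled power, equal strata.** λ = 1.960 + 0.842 = 2.802. Each stratum has 2.802 × √0.5 = 1.981, so p = 0.508. Disagreement = 2 × 0.508 × 0.492 = 0.500.

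| Pooled power | λ | Disagreement, 50/50 | Disagreement, 70/30 |
|---|---|---|---|
| 80% | 2.80 | 50% | 55% |
| 90% | 3.24 | 47% | 54% |
| 95% | 3.60 | 40% | 50% |
| 99% | 4.29 | 24% | 36% |
| 99.9% | 5.05 | 10% | 22% |
| 99.99% | 5.68 | 4% | 13% |

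The 95% row is close to what the article's own formula gives if the 210 enrolled form two equal groups of 105: 5 / (10 × √(2/105)) = 3.62, or 95% power at a standard deviation of 10.

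**Interaction test on the same data.** The slope difference is divided by its own standard error. With equal true slopes it is declared non-zero in 5% of studies by construction. In simulation (400,000 draws for each combination of 80% or 90% power with a 50/50 or 70/30 split) the rate was 4.95% to 5.03%.

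**Power of the interaction test.** With equal strata, the standard error of the slope difference is twice that of the pooled slope. An interaction as large as the main effect therefore has noncentrality λ/2. At 80% main-effect power this is 1.40, which gives 29% power.

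**The case against.** The strongest reply is that the article never says strata will be judged by their own p-values. Stratified estimates can be compared by their intervals or by a formal contrast, and such a contrast could sit in an analysis plan that is not shown. A reader might infer that the plan commits to reading significant in one stratum and not in the other as a difference. The text does not support that, so the percentages are conditional on that reading. What remains is that the article assigns this aim to stratification and names no between-stratum comparison anywhere.

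Second, the 80% power belongs to a two-group difference of 5 bpm. The heat slope for heart rate comes from continuous wearable records over 12 weeks a year for three years, and its power could be far higher. This stands. A reader might infer that equal effects will often look different whatever the power, but the lower rows of the table show otherwise. For heart rate, frequent disagreement is not established.

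Third, none of the four hypotheses concerns age or gender, the wording is exploratory, and the article describes a feasibility phase. This stands too and limits how much is at stake. It does not remove the need for an estimate of the difference, since even an exploratory comparison needs one with its uncertainty.

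Finally, figures for particular age bands or age-by-gender cells would describe a design the article does not give, so none are used here.

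**Conclusion.** The point holds in a limited, conditional form. The method named for age and gender differences estimates effects within strata and gives no estimate or test of the difference, and nothing else in the article supplies one.

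If strata are read by their own significance, equal slopes would look different in about 40% to 55% of studies at 80% to 95% pooled power (two strata, 50/50 to 70/30). With equal strata the rate is about 24% at 99% and 10% or less from 99.9% upward; uneven strata stay higher. An interaction test holds the rate at 5%.

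These figures rest on assumed pooled power and stratum shares and on a normal approximation. Repeated measures and clustering by village are not modelled. The risk is greatest for outcomes measured less precisely than heart rate. It is a weakness in an exploratory analysis and does not affect the study's main hypotheses.

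**What to change.** In the Data analysis section, state that age and gender differences in the heat effect will be judged by heat × gender and heat × age terms, with age continuous, in the mixed model fitted to all farmers. Report each as the difference in slope (for age, the change in slope per unit of age) with its 95% confidence interval, and label it exploratory. Keep stratum-specific estimates as description only.

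The cost is a sentence or two of wording and no new data. The real downside is imprecision: with 80% power for the main effect and equal strata, an interaction as large as the main effect is detected with about 29% power, so fewer differences will be claimed. That imprecision is already in the data. The interaction interval shows it, whereas separate stratum verdicts hide it.

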**Figure 5. f0005:**
[figure not shown]
Overview of exposure and outcome variables within the Heat to Harvest (H2H) study, and their sequential and cascading framework.

**Table 1. t0001:** Overview of pathways, outcomes and exposure with corresponding measured variables.

	**Pathway**	**Measured variable**	**Functional form**
Exposure	Heat	– Indoor temperature and humidity	– continuous
		– Outdoor climate conditions (air temperature, rainfall, wind speed, wind direction, solar radiation, humidity)	– continuous
Outcome	Physiological response and work capacity	– Wearable data (heart rate, energy expenditure, activity levels, sleep)	– continuous
		– GPS data (farmers work itineraries and time allocation)	– spatiotemporal data
Outcome	Harvest yield	– Remote sensing data (vegetation indices)	– raster
		– Field boundaries measured with GPS devices (locations of crop fields)	– point data
Outcome	Nutritional status	– Anthropometric measurements (weight, height measurements of children < 5 years)	– continuous

#### Structural equation modeling (SEM) and mediation analysis

To assess both direct and indirect effects of heat exposure, the study will employ Structural Equation Modeling (SEM) with mediation analysis. This approach enables the simultaneous estimation of multiple pathways linking heat exposure to physiological stress, work capacity, harvest yields, and child nutrition, providing a comprehensive understanding of the cascading impacts of heat stress.

Direct effects will be assessed by evaluating the independent influence of heat exposure on physiological stress (e.g. heart rate, energy expenditure), work capacity (e.g. labor duration, frequency of rest breaks), and child nutritional status. These analyses will offer insights into the immediate physiological and occupational impacts of heat and their direct links to health outcomes in children.

Beyond direct effects, SEM will estimate indirect pathways through which heat exposure impacts agricultural productivity and child nutrition. The central hypothesis posits that heat exposure induces physiological stress, which subsequently reduces work capacity, leading to decreased harvest yields and, ultimately, to poorer nutritional outcomes in children. Mediation will be tested using specific pathway models, such as:
Heat exposure → Physiological stress → Reduced work capacityHeat exposure → Reduced work capacity → Lower harvest yields → Poorer child nutrition

To quantify the role of mediating variables, indirect effects (e.g. via work capacity) will be compared with total effects (the overall impact of heat exposure on child nutrition), allowing for estimation of the relative contribution of different pathways.

To ensure the validity and robustness of the SEM, model fit will be assessed using multiple indices, including the Chi-square test, Comparative Fit Index (CFI), Tucker-Lewis Index (TLI), and Root Mean Square Error of Approximation (RMSEA). Through this rigorous analytical framework, the study aims to generate reliable and generalizable evidence on how heat stress affects the livelihoods and health of subsistence farming households.

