**What is the impact of heat exposure on the physiological responses of farmers?**
**Hypothesis 1**: Increased heat exposure will significantly elevate physiological strain, as measured by heart rate and body temperature.**How does heat exposure influence farmers’ work capacity and farming behaviors?**
**Hypothesis 2**: Higher temperatures will reduce work capacity and alter farming behaviors, including daily activity patterns, sleep quality, duration, and energy expenditure.**What is the relationship between heat exposure, work capacity, health, and farming practices on harvest yields?**
**Hypothesis 3**: Heat exposure will lead to reduced harvest yields by impairing farmers’ work capacity and health.**How do these factors indirectly affect the nutritional status of children under five in farming households?**
**Hypothesis 4**: Reduced work capacity and lower harvest yields due to heat exposure will negatively impact child nutrition.

This study systematically investigates these pathways using wearable sensors, GPS tracking, offering valuable insights into climate-related challenges faced by subsistence farmers and their families.

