#### Physiological response and work capacity (health impact pathway 2)

To monitor farmers’ physiological responses to heat exposure, the study will deploy two types of wearable devices to enable continuous, high-resolution data collection. All participants will wear the Garmin Vivosmart 5, which records heart rate, step count, and sleep metrics, including duration and quality. This device will be worn throughout the study period to provide real-time data on physiological strain. Additionally, a subset of participants will wear the Activinsights GENEActiv Original, a high-resolution actigraphy device that records gross motor activity and sleep at 10 hz, providing complementary data to the Vivosmart 5. To distinguish between heart rate changes due to physical exertion and those due to heat exposure, the analysis will incorporate methodological corrections, including adjustments for cardiac drift.

To assess work capacity, daily activity, and rest behavior, the study will monitor key indicators such as time engaged in fieldwork, distance traveled, and frequency and duration of rest periods. Each participant will use a Renkforce GP-102 Porter GPS tracker for a minimum of 20 days during the harvest season, capturing spatial and temporal data on labor patterns. GPS data will be stored locally and synchronized offline by field workers at scheduled intervals.

Prior to deployment, compatibility testing will be conducted to ensure that concurrent use of multiple wearable devices does not result in signal interference. Charging logistics will be optimized by providing participants with power banks and foldable solar panels, enabling overnight charging and minimizing disruptions to continuous data collection.

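### Energy expenditure is named as a marker of the SEM's stress mediator, but elsewhere it is a behaviour altered by heat and, in the only computation given, is built partly from the data that define work capacity

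*Protocol article*

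**What the plan says.** **Role in the SEM.** The section on structural equation modeling and mediation analysis lists direct effects of heat, including its "independent influence of heat exposure on physiological stress (e.g. heart rate, energy expenditure), work capacity (e.g. labor duration, frequency of rest breaks". Energy expenditure stands beside heart rate as an example of stress, and rest breaks are an example of work capacity. The central hypothesis there is that "heat exposure induces physiological stress, which subsequently reduces work capacity". The first mediation chain named runs from heat through stress to lower work capacity.

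**Role in the hypotheses.** Hypothesis 1 reads: "Increased heat exposure will significantly elevate physiological strain, as measured by heart rate and body temperature". Hypothesis 2 reads: "Higher temperatures will reduce work capacity and alter farming behaviors, including daily activity patterns, sleep quality, duration, and energy expenditure". Energy expenditure appears only in the second.

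**Source.** The Abstract, Table 1 and the Expected results section on work capacity present energy expenditure as wearable data. The data-analysis section for health impact pathway 2 brings in the GPS logger to improve its assessment, "allowing for the estimation of energy expenditure based on distance traveled, travel speed, terrain changes, and rest intervals". No other computation is described.

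**Work capacity.** The measurement section for pathway 2 uses "key indicators such as time engaged in fieldwork, distance traveled, and frequency and duration of rest periods", and for the labor patterns states: "Each participant will use a Renkforce GP-102 Porter GPS tracker for a minimum of 20 days during the harvest season".

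**The concern.** A mediator has to be something other than the outcome it is meant to explain. Energy expenditure estimated from how far and how fast a farmer moved, and how long the farmer rested, is to a large extent a record of how much work was done. Used as the stress marker, it places work on both sides of the stress-to-work path.

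The expected sign is also doubtful. The hypothesis has heat raising stress and stress lowering work. A farmer who stops early in the heat has lower movement-based energy expenditure, and on that marker alone is scored as less stressed. Both legs of the chain could then be reversed. The product of two reversed legs is still negative, so the indirect effect on its own would look like support for the hypothesis.

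At stake is how the first named mediation chain is read: whether heat reduces work through physiological strain, or directly, for example by farmers choosing to stop.

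**Working it through.** **1. Side-by-side reading.** No figure in the protocol depends on this point, so the first check is textual.

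| Place in the protocol | Role or source of energy expenditure |
|---|---|
| Background, Hypothesis 1 | Not among the strain measures |
| Background, Hypothesis 2 | Behaviour altered by heat |
| SEM section | Example of stress (mediator) |
| Abstract, Table 1, Expected results | Wearable |
| Data analysis, pathway 2 | GPS logger: distance, speed, terrain, rest |
| Measurements, pathway 2 | Not listed among what the wristband worn by all participants records (heart rate, steps, sleep) |

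Two of the four GPS inputs, distance and rest, are also work-capacity indicators in the measurement section. Rest breaks are in addition a work-capacity example in the SEM section. Table 1 puts physiological response and work capacity in one row, so it does not separate mediator from outcome.

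**2. Closed form under no true mediation.** The effect sizes and correlations are assumptions; the protocol gives none.

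- Heat H acts on work W directly: W = −cH + e, with c = 0.3.
- Energy expenditure is a noisy measure of work: EE = W + u, with u independent of H and e.
- Let r be the correlation of EE and W given H. Then r² = var(e) / [var(e) + var(u)].
- Heat-to-EE slope: −c = −0.3.
- EE-to-W slope, holding H: cov(W, EE | H) / var(EE | H) = var(e) / [var(e) + var(u)] = r².
- Indirect effect: −c × r². Total effect: −c. Apparent share mediated: r².

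| Assumed r | Indirect effect (−0.3 × r²) | Apparent share mediated | True share |
|---|---|---|---|
| 0.5 | −0.075 | 25% | 0% |
| 0.7 | −0.147 | 49% | 0% |
| 0.8 | −0.192 | 64% | 0% |
| 0.9 | −0.243 | 81% | 0% |

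**3. Simulation at the planned size.** This used n = 210 (the planned enrolment), 2,000 replicates, a standardised heat effect on work of −0.3 and no effect of stress on work. Here ρ is the overall correlation of EE and W. Given H it becomes r² = 0.91ρ² / (1 − 0.09ρ²), so at ρ = 0.5 the expected share is 0.2275 / 0.9775 = 23%, slightly below ρ².

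| ρ | Apparent share mediated | Runs with both legs significant |
|---|---|---|
| 0 | 0% | 0.1% |
| 0.3 | 8.5% | 27.5% |
| 0.5 | 23.1% | 59.3% |
| 0.7 | 46.5% | 86.2% |
| 0.9 | 79.7% | 98.3% |

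A comparison marker that responds to heat but is independent of work given heat gave a share of about 0%, with both legs significant in 4.8% to 5.6% of runs. The simulation treats each participant as one observation and ignores villages and repeated measures, so it shows the mechanism and does not predict the study's error rate.

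**The case against.** **The source may be the wearable.** This is the strongest objection. Three places say so, and the GPS estimate is introduced as an enhancement. A reader who sees only the GPS computation might infer that the whole stress path is circular by construction. The documents do not support that, because they never say which version enters the SEM. What remains is an unclear source, an overlap that is definite only for the GPS version, and a conflict with Hypothesis 2 whatever the source.

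**Both markers are examples.** Heart rate is named first, is the primary outcome and does not come from GPS. The problem therefore attaches to one indicator and not to the path as a whole. Still, energy expenditure is one of only two stress markers named, and the exertion adjustments in the protocol are stated for heart rate only.

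**Hypotheses 1 and 2 do not need this path.** A reader might infer that the conclusions on both would be artefacts. They would not be: Hypothesis 1 does not use energy expenditure, Hypothesis 2 concerns the effect of heat on work and behaviour, and the mixed models for pathway 2 relate heat directly to heart rate, activity and sleep.

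**Heart rate also rises with exertion.** The sample-size section says so. It is therefore not established that energy expenditure runs opposite to heart rate, and heart rate itself needs the planned exertion adjustment before it can serve as the stress marker.

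**The planned indirect-versus-total comparison is for child nutrition.** The r² figures concern the share of the heat effect on work. They are not the quantity that comparison would report.

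**The reversed legs would be visible.** This holds if each leg is examined separately. It is no safeguard if only the indirect effect is reported.

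**Conclusion.** The point holds in a limited form. The protocol gives energy expenditure two incompatible roles and two sources, and the one computation it describes shares distance and rest with the work-capacity indicators. To the extent that this variable serves as the stress mediator, the stress-to-work path partly relates work to itself and can show mediation that does not exist.

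The size depends on use. The r² result (25% to 81% for r of 0.5 to 0.9) is an upper illustration: it assumes energy expenditure is the sole mediator, equals work plus noise, and that there is no true mediation. The r values are assumptions. Alongside heart rate, or taken from the wearable, the distortion could be smaller; the documents do not allow it to be quantified.

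The consequence is confined to that SEM mediation path. The direct tests of Hypotheses 1 and 2 stand. The change is worth making before the SEM is specified, since it is specific and cheap and removes an avoidable bias.

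**What to change.** 1. In the SEM section, remove energy expenditure from the stress examples and treat it as a work-capacity or behaviour outcome, in line with Hypotheses 1 and 2.
2. State its source consistently in Table 1, the pathway 2 analysis section and Expected results. If both wearable and GPS estimates are kept, say which enters which model.
3. Split the combined physiological-response and work-capacity row of Table 1, and list each variable under one construct.
4. Represent stress in the SEM by markers not derived from the movement and rest data that define work capacity. Heart rate adjusted for concurrent step level from the wristband would serve, and it follows the exertion adjustment already planned in the sample-size and pathway 2 measurement sections.

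The cost is wording and the reassignment of one variable, with no new data. The small downside is that the stress construct then rests mainly on heart rate.
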